### Outcomes and measurement

The primary outcome is the total number of ADLA episodes during the 12-month follow-up period. ADLA episodes have been demonstrated to be a common complication of podoconiosis lymphoedema, occurring on average five times per year, and contributing to an average 4.4 days off work per episode [13, 17]. They are highly distinctive to patients, who in the study area, refer to these episodes as ‘*michader*’ (‘the blight that casts you down causing you to spend the night where it hit you’). Patients describe pain (in inguinal nodes or in the lower leg), swelling in addition to the ‘normal’ lymphoedema, and redness of the leg (sometimes as discrete longitudinal lines), chills (‘*birrd*’), anorexia and sometimes lower leg skin peeling towards the end of the episode. Considering most of the patients are unable to write, the trial team have designed the diary such that each patient marks a check mark (✓) or a dash (-) under the boxes corresponding to drawings showing a healthy patient (working in the field) and a patient experiencing acute attacks (shown in bed) for each day of the month. During the pilot phase, patients had no difficulty in marking the diaries based on their experiences of acute attacks. For the trial, patients will be trained to complete diaries at the outset and those who may have difficulty (including the elderly or visually impaired) will be requested to have their diaries filled by family members or neighbours who are able to read and write. In addition, diaries of patients in the immediate treatment group will be checked and collected at every monthly intervention meetings, whereas all diaries of patients in the control group will be checked for the first month and a random 10 % on subsequent months. Data collectors will discuss these diaries with patients at the quarterly data collection visit at home, and discrepancies between diary and recall will be reconciled.

All secondary outcomes will be measured following internationally validated scales where possible. Where no internationally validated scale is available, previously reported questionnaires will be used (Table 1).

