### Blinding

Given the nature of the intervention, the trial cannot be blinded. Although data collectors will be independent of those delivering treatment, they will be able to deduce the randomization status of participants when they see the supplies required for treatment. Similarly, statisticians conducting the analysis cannot be blinded. To minimise bias, an *a priori* analytical plan will be defined as the intervention is in progress and will be adhered to.

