### Intervention

The intervention in this trial is podoconiosis lymphoedema hygiene and foot-care management. This consists of monthly group meetings with instruction and practical demonstration of foot hygiene and foot care by Community Podoconiosis Assistants (CPAs), supporting daily self-treatment. In outline, ‘foot hygiene’ comprises soaking feet, washing with soap, rinsing with clean water, drying and application of emollient. ‘Foot care’ includes supervised use of single-layer, non-elastic bandages for disease stages ≥3; foot and calf exercises; instruction to practice foot hygiene daily at home; instruction to elevate the foot of the bed or areas slept on; instruction to use socks and shoes during waking hours. Those randomised to immediate treatment will receive a hygiene and foot-care intervention from December 2014 for one year, while those randomised to the control arm will be followed through 2014 and will be offered the intervention in 2015, unless it has been shown to be ineffective or harmful.

The trial interventions are described in Table 4.

**Table 4 Tab4:** Trial intervention

Action	Necessary items
Soak for 15 minutes	Bowl of water
Wash with soap	Named brand (GIV international white)
Apply emollient	Each patient will be issued with Whitfield’s ointment (2 tubes of 20 gm for a period of 1 month)
Apply bandages	For stage ≥3 disease; two short-stretch (<80 % stretch) bandages, spiral from foot, overlap 50 %, continue 8-10 cm above oedema
Elevation and exercises	Ankle rotation exercises.
	Elevate foot end of sleeping mattress, if used
Use socks and shoes	Temporary (tyre) shoes if bandages issued
	One pair robust, closed shoes and two pairs of socks after 3 months of treatment

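### The primary-outcome diary is checked and collected on a different schedule in each arm, which puts an unblinded, self-reported count at risk of differential ascertainment

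*Protocol article*

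**What the plan says.** Under Outcomes and measurement the endpoint is defined thus: "The primary outcome is the total number of ADLA episodes during the 12-month follow-up period". Patients, most of whom cannot write, mark a pictorial diary for each day of the month, with help from family or neighbours where needed.

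The same section then sets two procedures. For the treated arm, "diaries of patients in the immediate treatment group will be checked and collected at every monthly intervention meetings". For the other arm, "all diaries of patients in the control group will be checked for the first month and a random 10 % on subsequent months". No monthly collection is mentioned for controls. The Intervention section says the monthly meetings are led by the Community Podoconiosis Assistants (CPAs), who teach and demonstrate the foot care.

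One step is common to both arms: "Data collectors will discuss these diaries with patients at the quarterly data collection visit at home, and discrepancies between diary and recall will be reconciled". The Blinding section says these collectors are separate from the staff giving treatment, but that "they will be able to deduce the randomization status of participants". Statistical methods states that the main analysis tests the mean count by arm.

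**The concern.** An open trial with a patient-reported count depends on both arms being asked in the same way, equally often and by the same kind of person. Here the article writes the asymmetry in as a rule. From month 2 every immediate-arm diary is looked at each month, against about one control diary in ten. The immediate-arm check also takes place at the session where treatment is delivered.

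Two mechanisms pull in opposite directions. Closer checking may pick up more episodes in the immediate arm, which shrinks the apparent benefit. Handing the diary over at a treatment meeting may discourage patients from reporting attacks, which inflates it. Neither a larger sample nor a statistical analysis plan restores equal capture once the data are in. The only safeguard against bias that the Blinding section adds to collector independence is a prespecified analysis plan, and that does not act on measurement.

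**Working it through.** **1. The plan's own figure.** Inputs from Sample size: control mean 5.6, SD 4.9, reduction 28%, power 90%, α 0.05 (taken as two-sided), inflation 1.4, retention 0.85.

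- Difference = 0.28 × 5.6 = 1.568.
- n per arm = 2 × [4.9 × (1.960 + 1.282) / 1.568]² ≈ 205.2, rounded up to 206. This matches the article.
- 206 × 1.4 / 0.85 = 339.3, rounded up to 340 per arm, 680 in total. This also matches.

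The rounded difference 5.6 − 4.0 = 1.6 would give 198. That is rounding and does not affect this point.

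**2. Analysed number and standard error.** After 15% drop-out, 340 × 0.85 = 289 per arm. If the 40% allowance is wholly used up by confounder adjustment, the effective number is about 289 / 1.4 = 206. Both ends are shown.

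- SE = 4.9 × √(2/289) = 0.408
- SE = 4.9 × √(2/206) = 0.483

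**3. Effect of unequal recording.** The article gives no error rates, so the recording gaps below are assumptions. The SD is held at 4.9. The chance of a significant result favouring treatment is Φ(d/SE − 1.96), where d is the observed control-minus-immediate difference.

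(a) True means 5.6 and 4.0, controls under-record, immediate arm complete: d = 5.6 × c − 4.0, where c is the fraction of control episodes recorded.

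| Control recording | d | Power, 206 per arm | Power, 289 per arm |
|---|---|---|---|
| 100% | 1.60 | 91% | 98% |
| 95% | 1.32 | 78% | 90% |
| 90% | 1.04 | 58% | 72% |
| 80% | 0.48 | 17% | 22% |

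The difference disappears at c = 4.0 / 5.6 = 71%.

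(b) No true effect, immediate arm under-records, controls complete: d = 5.6 × (1 − t), where t is the fraction of immediate-arm episodes recorded.

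| Immediate-arm recording | d | False benefit, 206 per arm | False benefit, 289 per arm |
|---|---|---|---|
| 100% | 0 | 2.5% | 2.5% |
| 95% | 0.28 | 8% | 10% |
| 90% | 0.56 | 21% | 28% |
| 80% | 1.12 | 64% | 79% |

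**4. What the common step covers.** The quarterly visit gives both arms the same interviewer role and the same reconciliation. It does not make the inputs equal. Immediate-arm diaries have by then been checked every month, while most control diaries have not been checked since month 1. The recall set against them can reach back three months, and the person reconciling may know the arm.

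**The case against.** The strongest reply is that the article shows no bias. It reports no recording error, and the two mechanisms oppose each other. Attacks are described as highly distinctive to patients, all patients are trained, and the pilot found no difficulty with the diary. Table 3 schedules the diary at 3, 6, 9 and 12 months without separating arms, and the quarterly visit is made by people independent of treatment delivery. The abstract describes recall and diary as used together, so the monthly check is not the only route to the count. All of this stands, and it limits the point to a risk.

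Several stronger readings are tempting and are not supported:

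- A reader might conclude that the comparison is biased. The documents establish neither direction nor size.
- A reader might state that treatment staff check the diaries. The article gives the venue but does not name the checker, so CPA handling is an inference.
- A reader might say that control diaries stay at home for three months and are filled in from memory. How control diaries are collected is not stated, and a condensed article may leave that to the procedures.
- A reader might say that controls are only spot-checked. All control diaries are checked in month 1.
- A reader might say that nothing can be learned afterwards. The control subset is random, so comparing checked with unchecked control diaries would inform the effect of checking in that arm. It would not show whether contact at treatment meetings suppresses reporting.

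The reply does not explain why the schedules must differ, and none of it makes them equal.

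**Conclusion.** The point holds as a risk of differential ascertainment, direction undetermined, that arises from a stated arm-specific rule. The common quarterly visit mitigates it in part.

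The figures show how sensitive the trial is to an assumed error. They do not measure an error in it. A recording gap of 5 to 10% moves the observed difference by 0.28 to 0.56 episodes a year in the two scenarios above, against a planned effect of about 1.6. At 10%, power falls to 58–72% in one direction, or the false-benefit rate rises to about 21–28% in the other. These results assume SD 4.9, two-sided α 0.05, a normal approximation, 206 to 289 analysed per arm, and under-recording confined to one arm.

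**What to change.** Apply one diary procedure to both arms, namely the schedule now given for controls: all diaries checked in month 1 and a random 10% in each later month. State that every diary is collected at the quarterly home visit. Have the same data collectors, independent of treatment delivery, do this in both arms, and take diary checking and collection out of the intervention meetings. The adverse-event questions asked at those meetings are a separate matter and need not change.

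At the quarterly visit, record the diary as marked before recall is discussed. Use those entries in a sensitivity analysis alongside the reconciled count. Making the unreconciled marks the primary endpoint is not recommended, because most patients cannot write and reconciliation gives some protection against missed or wrongly marked days.

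Cost: protocol and procedure wording, and a modest shift of work to data collectors (340 immediate-arm checks in month 1, then about 0.10 × 340 = 34 a month). Immediate-arm diaries may be slightly less complete. Recruitment began on 8 October 2014, so the change may reach only the remaining follow-up. The date of the switch should then be recorded so that diary months under each procedure can be told apart.

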**Methods/Design:**

This is a pragmatic, individually randomised controlled trial. We plan to randomly allocate 680 podoconiosis patients from the East Gojjam Zone in northern Ethiopia to one of two groups: ‘Standard Treatment’ or ‘Delayed Treatment’. Those randomised to standard treatment will receive the hygiene and foot-care intervention from May 2015 for one year, whereas those in the control arm will be followed through 2015 and be offered the intervention in 2016. The trial will be preceded by an economic context survey and a Rapid Ethical Assessment to identify optimal methods of conveying information about the trial and the approaches to obtaining informed consent preferred by the community. The primary outcome will be measured by recording patient recall and using a simple, patient-held diary that will be developed to record episodes of acute attacks. Adherence to treatment, clinical stage of disease, quality of life, disability and stigma will be considered secondary outcome measures. Other outcomes will include adverse events and economic productivity. Assessments will be made at baseline and at 3, 6, 9 and 12 months thereafter.

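### Diary and recall are reconciled at visits by staff who can tell the arm, so this step can change the primary ADLA count; Table 3 schedules no recall after baseline

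*Protocol article*

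**What the plan says.** Outcomes and measurement defines the endpoint: "The primary outcome is the total number of ADLA episodes during the 12-month follow-up period". The diary carries a mark "for each day of the month", so it records days, while the endpoint counts episodes.

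On the source of the count:
- The Abstract states: "The primary outcome will be measured by recording patient recall and using a simple, patient-held diary". It gives no order between the two sources.
- Outcomes and measurement states: "Data collectors will discuss these diaries with patients at the quarterly data collection visit at home", and continues that "discrepancies between diary and recall will be reconciled".
- Table 3 (Study visits) marks the ADLA recall row at enrolment and baseline only. The ADLA diary row is marked at 3, 6, 9 and 12 months.

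On who is present, the Blinding section says "data collectors will be independent of those delivering treatment", but also that "they will be able to deduce the randomization status of participants when they see the supplies required for treatment".

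Outcomes and measurement also sets different monthly checks. In the immediate arm every diary is checked and collected each month. In the control arm all diaries are checked in month 1, and a random 10% in each later month.

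**The concern.** The trial is open-label, and its single primary endpoint is reported by the patient. Between the patient's mark and the analysed count, the protocol places a conversation after which the record may change. The staff in that conversation can tell the arm from the supplies in the home. If doubtful attacks are kept more readily in one arm than in the other, the difference enters the mean count directly. An analysis plan fixed in advance acts only after that point. It could recover the patient's own marks only if they were kept and entered, which the article does not say.

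The conflict over the source adds to this. A case report form built from Table 3 would have no follow-up recall field. One built from the Abstract or from Outcomes and measurement would need one. Where both sources exist, the article does not say which prevails.

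**Working it through.** **Placing the statements side by side.** The Abstract and Outcomes and measurement are compatible: both use recall and diary for a count that accrues in follow-up, and only the latter mentions reconciliation. Table 3 differs from both, since it has no recall entry after baseline. The conflict is thus one table against two passages of text.

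**Inputs.** From Sample size: mean 5.6 and SD 4.9 episodes per year, a 28% reduction, alpha 0.05, power 90%, 206 per group before inflation, 340 per group after it, 15% drop-out. Assumed here: a two-sided test, and the size of the counting difference, for which the documents give no figure.

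**The plan's own figure.** With a difference of 0.28 × 5.6 = 1.568:

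n = 2 × [4.9 × (1.960 + 1.282) / 1.568]² = 205.2, rounded up to 206 per group.

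206 × 1.4 / 0.85 = 339.3, so 340 per group and 680 in total. The stated figures reproduce with a two-sided test. (The rounded means, a difference of 1.6, would give 198.) The sample size is not at issue.

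**Effect of an arm-dependent count when there is no true effect.** Evaluable patients: 340 × 0.85 = 289 per arm. SE = 4.9 × √(2/289) = 0.408. For a shift s, the two-sided rejection probability is

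1 − Φ(1.96 − s/SE) + Φ(−1.96 − s/SE).

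| Assumed relative difference | Shift s (episodes) | Share of planned 1.568 | Rejection rate, 289 per arm | Rejection rate, 206 per arm |
|---|---|---|---|---|
| 0% | 0 | 0% | 5.0% | 5.0% |
| 5% | 0.28 | 18% | 10.6% | 8.9% |
| 10% | 0.56 | 36% | 27.9% | 21.3% |
| 15% | 0.84 | 54% | 54.0% | 41.3% |

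The 206 column uses SE = 4.9 × √(2/206) = 0.483 and serves as a lower bound on the information available.

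**The opposite direction.** Take the planned means of 5.6 and 4.0, with treated-arm episodes over-counted by 10%. The observed difference is 5.6 − 4.4 = 1.2 instead of 1.6. Power falls from 97.5% to 83.7% at 289 per arm, and from 91.2% to 70.0% at 206 per arm.

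**The case against.** - **Table 3 can be read charitably.** The recall row may be the history taken before diaries exist, and the diary row may stand for the visit at which the diary is discussed. That is plausible and makes the conflict small. It does not remove it, because the text has recall compared with the diary in follow-up and the table provides no place for it. A reader might infer that three places give three different sources; they do not.
- **The text does not say who decides.** A reader might infer that data collectors settle the count and overwrite the diary. The sentence on reconciliation is passive. It neither names the decision-maker nor says that original marks are altered. The diaries are physical records, and the protocol provides for source data verification and a monitoring plan. This stands: the documents support a step that can change the count and takes place with arm-aware staff, and no more than that.
- **The rule turning days into episodes may sit in the SAP or the standard operating procedures.** This stands, and its absence from an article is not a finding. A reader might also infer that episode numbers are decided in the home conversation, but the article does not say so. Nor can the 4.4 days in Outcomes and measurement be used to estimate how many attacks span two months. That figure is days off work, and spanning a month end would affect both arms.
- **Safeguards are stated.** Collectors are separate from treatment staff, an analysis plan is fixed in advance, and attacks are described as distinctive to patients. These reduce the risk. They do not conceal the arm during reconciliation.
- **Using unreconciled marks could do harm.** While one arm is checked in full each month and the other at 10% after month 1, unreconciled diaries would not be comparable between arms. This stands, so the fix must include equal checking.

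**Conclusion.** The concern holds in a limited form. The protocol describes a non-blinded step that can change the sole primary count, does not say which source prevails, and contradicts its own visit schedule on whether recall is collected after baseline.

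It would go too far to read this as demonstrated bias in favour of treatment. Neither size nor direction is documented, and a shift the other way would cost power. The false-positive rates of about 11% to 54% at 289 per arm rest on an assumed 5% to 15% relative counting difference, no true effect, a common SD of 4.9 and the normal approximation. They show how sensitive the test is, not what will happen. They do show that a modest counting difference matters: 10% is 0.56 episodes, roughly a third of the planned effect.

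**What to change.** 1. Enter and keep the diary marks as they stand before any discussion at the quarterly visit.
2. Record quarterly recall in both arms in a separate field that never overwrites the diary.
3. Name the diary as the prevailing source for the primary count.
4. Derive episodes from the day marks by one prespecified rule, applied without knowledge of arm. The rule itself can sit in the SAP or the standard operating procedures.
5. Keep the reconciled count as a separate variable and report it as a sensitivity analysis.
6. Use the same monthly diary-checking rate in both arms. Without this, step 3 would compare checked diaries with mostly unchecked ones.
7. Align the Abstract, Table 3 and Outcomes and measurement.

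The cost is mainly case report form and procedure wording plus a derived variable. Equal checking is the larger item. With 340 controls, 10% is 34 diaries a month, so full checking in both arms means up to 306 more per month; a common lower rate avoids that. Some marking errors will stay uncorrected in the primary count and add some noise. Patients' own unblinded reporting is not addressed. Trial status says that recruitment has begun, so diaries already discussed should be checked for whether the original marks survive on paper.

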### Safety

This is a pragmatic trial of hygiene and foot-care interventions that use household and community care-based products that are not prescription medical products and thus are associated with few safety concerns. Nonetheless, safety will be carefully monitored to confirm that there is indeed minimal risk. Adverse events in both arms will be reported on the case record forms completed by the data collectors at the quarterly home visits. Adverse events related to the intervention will be actively elicited from those randomised to immediate treatment by CPAs at the monthly meetings via specific questions. The study coordinator will then confirm occurrence of events, analyse them and report them by telephone and email within 24 hours to the Local Safety Monitors (LSMs), and the investigators who will reach a consensus on whether a Serious Adverse Event (SAE) needs further defining as a Suspected and Unexpected Serious Adverse Reaction (SUSAR) based on the type of event, the relationship of the event to the time of administration and the known biology of intervention. However, adverse events, regardless of relation to the intervention, will receive treatment accordingly. Any SUSAR will then be reported within 24 hours of detection to the Trial Steering Committee, Institutional Review Boards (IRBs), ethics committees and regulatory authorities in Ethiopia and the United Kingdom.

### Adverse event monitoring

We conducted a risk assessment for this trial and considered whether a Data Safety Monitoring Board (DSMB) was required. The reason for putting a DSMB in place is to monitor safety and efficacy outcomes and consider whether the trial needs to be revised or stopped early. We concluded that safety events are too unlikely to indicate that a DSMB should monitor events. On considering efficacy and whether an interim analysis would be appropriate to assess whether the question has been answered earlier than predicted, we also concluded this was unnecessary. We consider that ending the trial early following a DSMB assessment of an interim analysis would be essentially meaningless in this setting because as of yet, this intervention is not available to the population, and therefore, we would be better continuing the trial to its full power in order to obtain a full data set to support analysis of the primary and secondary endpoints. Therefore, based on recommendations in articles on when a DSMB is required, we have put local independent safety monitors in place who will review all SAEs immediately on being notified by the study team and review all adverse events monthly [18, 19].

We anticipate that the hygiene and foot-care intervention will bring clinical improvements to the lower legs and social and quality of life changes to the patient as a whole. These will be recorded as part of the assessment of scientific objectives. Symptom enquiry related to the primary outcome (ADLA) will also create the opportunity to identify unexpected systemic effects of the intervention.

The standard of comparison or the control arm is delayed intervention. If the trial shows benefit with this intervention, the data will then be used to influence policy in Ethiopia, and elsewhere, to make this intervention widely available.

